## Abstract

**Introduction:**

Dry eye disease (DED) is a chronic disorder of the ocular surface (OS) that is influenced by a variety of factors, resulting in ocular discomfort and visual impairment. Studies have also shown that dry eye syndrome detrimentally impacts patients’ sleep quality (SQ), mental well-being, and overall mental health. This SPIRIT- and STRICTA-compliant protocol describes a multicenter, single-blind randomized controlled trial designed to evaluate the efficacy and safety of acupuncture combined with auricular acupressure compared with 0.1% sodium hyaluronate eye drops in adults with DED.

**Methods and analysis:**

A total of 126 patients with DED will be recruited and randomly assigned to one of two groups at a 1:1 ratio across three centers. Participants in the intervention group will receive acupuncture combined with auricular acupressure for 8 weeks, whereas the control group will be treated with 0.1% sodium hyaluronate eye drop. Following the intervention, an eight-week follow-up will be conducted. Primary outcome is the Ocular surface disease Index (OSDI). Secondary outcomes are Breaking up time (BUT), Conjunctival Impression Cytology (CIC), cornea fluorescein staining (CFS), Tear meniscus height (TMH), Meibum quality score (MQS), Meibomian gland score (MGS), Meiboscore, Function of the meibomian gland, Pittsburgh Sleep Quality Index (PSQI), Self-rating depression Scale (SDS), and Self-rating anxiety scale (SAS). The primary endpoint is the change in OSDI score from baseline to week 8, and the primary effect measure will be the adjusted between-group mean difference, estimated using a linear mixed-effects model. This study will assess whether acupuncture combined with auricular acupressure improves symptoms of dry eye and affects sleep and mood compared with sodium hyaluronate.

**Clinical trial registration:**

https://itmctr.ccebtcm.org.cn, Identifier ITMCTR2024000673.

## Introduction

1

DED is a widespread ocular condition necessitating prompt diagnosis and thorough therapeutic management. The 2020 Chinese Expert Consensus on Dry Eye (1) describes DED as a chronic OS disorder stemming from multiple etiological factors. This ailment may trigger a variety of ocular discomforts and visual deficits due to tear film instability or disruptions in the OS microenvironment. Common manifestations of DED include redness, eye fatigue, tingling sensations, dryness, a feeling of a foreign body, and compromised vision (2). According to the TFOS Dry Eye Workshop II and the updated TFOS DEWS III, the global prevalence of DED ranges widely and continues to increase, particularly among aging populations and women (3). Notably, the prevalence of DED escalates with age and predominantly affects women more than men, with an onset age that is decreasing (4, 5). DED adversely impacts the quality of life (QoL) and productivity, increasing both familial economic strains and the demands on healthcare systems (6).

Tear film instability, hyperosmolarity, inflammation, and cellular damage are acknowledged as the primary pathological mechanisms driving the adverse cycle associated with DED (1). The aim of DED treatment is to restore OS and tear film homeostasis by disrupting this cycle (7). Conventional therapies typically encompass a variety of artificial tears, eyelid margin hygiene practices, meibomian gland massages, intense pulsed light therapy, thermotherapy, or thermal pulsation, and may extend to topical or systemic anti-inflammatory treatments and surgical procedures (8, 9). Nevertheless, these methods are frequently criticized for their prohibitive costs, limited efficacy in symptom alleviation, and transient beneficial effects.

Acupuncture is widely recognized as a form of complementary and alternative medicine that involves inserting fine needles at specific points known as acupuncture points. Numerous clinical trials have shown that acupuncture is effective for various ophthalmic disorders, including acute hordeolum, diabetic retinopathy, glaucoma, and myopia (10–12). It is also a well-established treatment for DED (13), typically targeting key acupoints such as BL2, EX-HN5, BL1, SJ23, SP6, GB20, ST2, and ST36. Studies comparing systemic versus local acupoint selection (14) have shown that whole-body acupoint therapy is more effective.

Evidence supporting acupuncture for DED originates from multiple levels, including animal mechanistic studies, small to medium-sized randomized controlled trials, and systematic reviews. Animal studies (15, 16) suggest that acupuncture may modulate lacrimal gland secretion, inflammatory cytokines, and neurosensory function; however, these findings cannot be directly extrapolated to clinical efficacy. Several RCTs and meta-analyses (17, 18) report improvements in tear film stability and patient-reported symptoms compared with artificial tears, yet heterogeneity in study design, sample size, and outcome measures remains substantial, underscoring the need for rigorously designed multicenter trials.

Auricular acupressure, a technique related to acupuncture within Traditional Chinese Medicine (TCM), involves stimulating auricular points by adhering dried seeds of vaccaria segetalis to achieve the desired effect (19). The French physician [name] (1908–1996 AD), invented and promoted auriculotherapy, and pioneered the auricular mapping of the embryo’s reflection. Based on this work, Chinese acupuncturists developed ear acupuncture (20). Auricular acupressure has been proven effective in analgesia, anti-vomiting, emotion regulation (21–23), and other aspects, including DED. It targets specific auricular points such as Mu1 (TG2b) and Mu2 (AT1b) to treat DED by elevating hormones levels and regulating the sympathetic nervous system (24). This approach has proven effective for DED, both as a standalone treatment and in combination with artificial tears or electrical stimulation (25).

In addition, the impact of DED on QoL and associated mood disorders such as depression and anxiety is increasingly recognized. Chronic discomfort and pain from DED can negatively influence patients’ sleep, mood, and overall mental health (26), potentially exacerbating the severity of DED (27). In this trial, PSQI, SDS, and SAS are prespecified secondary outcomes, and analyses of these measures will be exploratory, as the study is powered for ocular symptom improvement assessed by OSDI. Researchers have found the beneficial effects of acupuncture and auricular acupressure in improving QoL and mental health (28). Bitar et al. (29) identified a strong link between DED and symptoms of anxiety and depression, proposing that effective treatments could also ameliorate these psychological issues. Therefore, we hypothesize that a combination of acupuncture and auricular acupressure might not only alleviate ocular surface symptoms but also effectively manage sleep and emotional issues in DED patients.

This multicenter, large-sample clinical, RCT is designed to assess the efficacy and safety of acupuncture combined with auricular acupressure in mitigating ocular symptoms and modulating mood and sleep among DED patients, while also ensuring the treatment’s safety and reliability through rigorous safety analyses and monitoring of adverse events.

## Methods and analysis

2

### Study design

2.1

This study is a multicenter, single-blinded, randomized controlled trial (RCT). Participants will be enlisted from three academic institutions: Third Affiliated Hospital of Zhejiang Chinese Medical University, Jiaxing Traditional Chinese Medicine Hospital, and Affiliated Optometry Hospital of Wenzhou Medical University. 126 patients will be enrolled and randomly assigned in equal proportions to the intervention or control group. Participants in the intervention group will undergo three 30-min sessions weekly over 8 weeks, whereas the control group will be treated with 0.1% sodium hyaluronate eye drop. Following the intervention, an eight-week follow-up will be conducted. Primary outcome is the Ocular surface disease Index (OSDI). Secondary outcomes are Breaking up time (BUT), Conjunctival Impression Cytology (CIC), cornea fluorescein staining (CFS), Tear meniscus height (TMH), Meibum quality score (MQS), Meibomian gland score (MGS), Meiboscore, Function of the meibomian gland, Pittsburgh Sleep Quality Index (PSQI), Self-rating depression Scale (SDS), and Self-rating anxiety scale (SAS). Evaluations will take place at weeks 0, 4, 8, 12, and 16. The enrollment schedule is illustrated in Table 1, and the flow chart of this trial is displayed in Figure 1. The completed trial will be reported in accordance with CONSORT 2010, including the extensions for non-pharmacologic treatments and harms reporting.

**Table 1 tab1:** The chart of enrollment and assessment.

Time point	Study period				
	Baseline	Treatment phase		Follow-up phase	
Enrollment	0 week	4th week	8th week	12th week	16th week
Eligibility screen	×				
Informed consent	×				
Medical history	×				
Randomization	×				
Intervention					
Experimental group		×	×		
Control group		×	×		
Assessment					
OSDI	×	×	×	×	×
BUT	×		×	×	
CIC	×		×	×	
CFS	×		×	×	
PSQI	×	×	×	×	×
SAS	×	×	×	×	×
SDS	×	×	×	×	×
TMH	×		×	×	
MQS	×		×	×	
MGES	×		×	×	
Meiboscore	×		×	×	
Lid margin abnormalities	×		×	×	
Safety					
VAS	×	×	×		

**Figure 1 fig1:**
[figure not shown]
Flowchart of the research procedures.

#### Ethics and dissemination

2.1.1

The protocol received endorsement from the Medical Ethical Committee of the Third Affiliated Hospital of Zhejiang Chinese Medical University, under the approval number ZSLL-KY-2023-049-01. Findings of the trial will be disseminated through peer-reviewed journals and scientific conferences.

#### Informed consent

2.1.2

The study will be ensured adherence to the Declaration of Helsinki formulated by the World Medical Association and relevant clinical research regulations in China. Consent for participation, manifested through the signing of the informed consent form, must be secured before randomization. Participants retain the right to withdraw from the trial at any time, with the reasons for withdrawal meticulously recorded.

### Participant recruitment

2.2

Recruitment began on December 12, 2024, and is expected to complete on December 20, 2025. Recruitment tactics will incorporate poster advertisements, community engagements, digital recruitment, and Ophthalmology outpatient services. Prospective participants will be briefed by their ophthalmologists regarding the study’s objectives, interventions, timeline, advantages, and potential risks at the designated hospitals. This will be followed by further verbal and written explanations from a local researcher. The trial is currently in the intervention phase with protocol version V3.0 and date December 2024.

#### Inclusion criteria

2.2.1

Participants who meet the following inclusion criteria will be eligible for the study:

Confirmed diagnosis of DED in line with the 2021 Chinese Expert Consensus on Dry Eye (30): having at least one subjective symptom (e.g., dryness, foreign body sensation, burning sensation, fatigue, discomfort, fluctuating visual acuity) and SIT≤5 mm/5 min or non-invasive tear film breakup time (NIBUT) ≤ 5 s, or having at least one subjective symptom and 5 mm/5 min < SIT≤10 mm/5 min or 5 s < NIBUT≤10s, together with positive CFS;Individuals aged 18 to 75 years, regardless of gender;Absence of systemic medication intake within the previous two weeks;Demonstrated capacity to cooperate during eye examinations and a commitment to participate in clinical observation trials;Execution of the written informed consent form for participation in the clinical trial.

#### Exclusion criteria

2.2.2

Participants who meet the following exclusion criteria will be excluded from the study:

Patients with hemorrhagic diseases;Inability to adhere to the designated follow-up protocol;Long-term users of sedatives, anti-depression, and anti-anxiety drugs;Pregnancy or lactation;Active ocular infection or inflammation unrelated to DED;Ocular surgery or trauma within the past 6 months;Severe meibomian gland dysfunction requiring procedural treatment;Contact lens use within the past month;Autoimmune diseases affecting the ocular surface.

### Randomization and blinding

2.3

The random allocation sequence will be generated using the computer-based random number generation function in SPSS 25.0, individuals assigned odd numbers will receive acupuncture, while those with even numbers will receive medication. An independent statistician will generate a permuted-block sequence stratified by center. Group assignments will be placed in sequentially numbered, opaque, sealed envelopes. Enrolling clinicians will open envelopes after consent. Given acupuncture’s unique nature, only single-blinding is achievable in this study. Distinct roles of operator, assessor, and statistician are delineated to ensure unbiased efficacy assessment and data collection, aiming to minimize potential biases as effectively as possible. Outcome assessors and statisticians will remain blinded to group allocation.

### Application selection

2.4

In this study, acupuncture needles are supplied by Huatuo, a brand produced by Suzhou Medical Supplies Factory, China. The manufacturer possesses a Manufacturer’s License Number: Su Drug Administration of Machinery Production 20,010,020 and a Registration Certificate Number: 20162200970. The needles come in two sizes: 0.18 × 25 mm and 0.25 × 40 mm. Ear press seeds are obtained from Shanghai TAICHENG Technology Development Co., Ltd. The sodium hyaluronate eye drops are from the Chinese brand Wanhan, holding a Chinese medicine approval No. H20203255. Comprehensive OS analyzer will utilize the MYAH ophthalmic optical biometry instrument from Topcon Healthcare Company, which is registered under Imported Medical Device Registration Number: 20232160188, and Product Serial Number: 172230032. The fluorescein sodium test strips are produced by Tianjin Jingming New Technological Development Co., Ltd. The manufacturer has a Manufacturer’s License Number: Jin Drug Administration of Machinery Production 20,100,040 and a Registration Certificate Number: 20222160497.

### Interventions and comparison

2.5

#### Intervention group

2.5.1

Participants will receive the acupuncture combined with auricular acupressure. Acupuncture will be conducted bilaterally at specific acupoints based on published literature and textbooks about acupuncture for ophthalmologic diseases or dry eye syndrome (31, 32): Taiyang (EX-HN5), Jingming (BL1), TongZiliao (GB1), Cuanzhu (BL2), Fengchi (GB20), Taixi (KI3), SanYinjiao (SP6), Guangming (GB37), ZuSanli (ST36), Hegu (LI4), and Taichong (LR3). The techniques include: targeting EX-HN5 toward the outer canthus to a depth of 0.6 inch, inserting BL1 along the orbital rim until soreness is felt, penetrating GB1 straight to 1.0 inch and then redirecting it flat toward the ear tip after inducing soreness and numbness, and aligning BL2 in the direction of BL1 up to 0.6 inch. GB20 will be aimed toward the ipsilateral inner canthus, incorporating lifting, inserting, and slight rotating until a radiating sensation is felt in the forehead or eyes. Smaller needles (0.18 × 25 mm) are designated for EX-HN5, BL1, GB1, and BL2, whereas larger needles (0.25 × 40 mm) are reserved for the remaining points to achieve the “De Qi” sensation. “De Qi”is defined as a composite sensation including soreness, numbness, heaviness, or distension perceived by the participant and confirmed by the practitioner. The therapy will occur thrice weekly for 8 weeks, each session lasting 30 min, culminating in 24 sessions. The number of needles per session will range from 10 to 14, depending on bilateral point selection. Adherence will be monitored through treatment logs, and auricular seeds will be checked and replaced every 2 days if detached. All procedures will be executed by acupuncturists with at least 3 years of experience, following standardized training. Acupoint locations are based on the 2010 World Health Organization (WHO) guidelines (ISBN:9787117123327) (Figure 2; Table 2).

**Figure 2 fig2:**
[figure not shown]
Location of acupoints.

**Table 2 tab2:** Location of acupoints.

Acupoints	Location
Taiyang (EX-HN5)	In the region of the temples, in the depression about one fingerbreadth posterior to the midpoint between the lateral end of the eyebrow and the outer canthus.
Jingming (BL1)	In the depression superior to the inner canthus.
TongZiliao (GB1)	0.5 cun (Chinese inches) lateral to the outer canthus on the lateral side of the orbit.
Cuanzhu (BL2)	On the face, in the depression on the medial end of eyebrow, on the supraorbital notch.
Fengchi (GB20)	On the nape, below the occiput, in the depression between the upper portion of m. sternocleidomastoideus and m. trapezius.
Taixi (KI3)	Posterior to the medial malleolus, in the depression between the tip of the medial malleolus and tendo calcaneus.
Guangming (GB37)	5 cun (Chinese inches) above the tip of the lateral malleolus, on the anterior border of the fibula.
Hegu (LI4)	Located on the dorsum of the hand, between the 1st and 2nd metacarpal bones, in the middle of the 2nd metacarpal bone on the radial side.
Sanyinjiao (SP6)	Located on the inner side of the lower leg, 3 cun (Chinese inches) above the tip of the medial malleolus, just behind the posterior border of the tibia.
Zusanli (ST36)	3 cun (Chinese inches) below the lateral eye of the knee, at a point one horizontal finger’s width from the outer edge of the anterior tibial crest.
Taichong (LR3)	On the dorsum of the foot, in the depression proximal to the first metatarsal space.

Post-acupuncture, auricular acupressure will be applied and maintained for 2 days at points based on findings from previous studies (31, 33), including Eye (LO5), Heart (CO15), Liver (CO12), Spleen (CO13), Lung (CO14), Kidney (CO10), Occiput (AT3), Shenmen (TF4), and Endocrine (CO18). Participants will be instructed to press each auricular point 3–5 times per day, with each pressing lasting approximately 30–60 s. The intensity of stimulation will be standardized as a moderate, tolerable sensation, characterized by local soreness, distension, or warmth without causing pain. Participants will be instructed to avoid excessive force and to discontinue pressing if significant discomfort occurs. Auricular seeds will be replaced at the subsequent treatment session (Figure 3).

**Figure 3 fig3:**
[figure not shown]
Location of auricular points.

#### Control group

2.5.2

Participants will receive 0.1% sodium hyaluronate eye drops (Wanhan), administered four times daily, one drop per eye, continuously for 8 weeks. Researchers will provide standardized instructions for eye drop application to ensure correct usage (33).

Both groups will abstain from glucocorticoids, nonsteroidal anti-inflammatory drugs, and related hormonal eye drops during the study. Use of additional lubricants is clarified and will be recorded. All concomitant medications will be meticulously recorded in the Case Report Form (CRF), noting the drug name, total daily dose, intended use, start and end dates, and usage status at the study’s conclusion. This trial adopts an active comparator rather than sham acupuncture, reflecting a pragmatic effectiveness design intended to evaluate the comparative benefit of acupuncture combined with auricular acupressure against commonly used standard therapy. This approach prioritizes clinical relevance and external validity, while acknowledging the potential influence of expectancy effects.

#### Sample size

2.5.3

The sample size is based on the between-group difference in OSDI at week 8, and that longitudinal correlation is handled analytically via LMMs. According to the previous study (34), A 10-point reduction is adopted as the minimal clinically important difference (MCID). We assumed an SD = 18 for change in OSDI when powering the study based on previous experiment design (35). Thus, substituting *σ* = 18, *Δ* = 10, with two-sided *α* = 0.05, power = 80%, and a 20% attrition allowance, utilizing the formula: 
$n=\frac{2\sigma^{2}{\left(Z_{1-\alpha /2}+Z_{1-\beta }\right)}^{2}}{\Delta^{2}}.$
 We calculated that 63 cases will be needed in each group, totaling 126. Each of the three sub-centers will recruit 21 participants for both the control and treatment groups.

### Outcome measures

2.6

All outcome measures and their corresponding assessment timelines are specified in Table **1**, and the research protocol is depicted in Figure 3. Patients are required to abstain from using eye drops 4 hours before tests to prevent any immediate effects.

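### The 4-hour pre-test rule removes immediate effects of the assigned treatment in the eye-drop arm only, and ear seeds are likely to show the allocation to the live examiner at week 8

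*Protocol article*

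**What the plan says.** All references are to the protocol article.

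- **Pre-test rule (2.6 Outcome measures).** "Patients are required to abstain from using eye drops 4 hours before tests to prevent any immediate effects". No other interval between treatment and testing is given.
- **Control treatment (2.5.2).** Sodium hyaluronate drops, "administered four times daily, one drop per eye, continuously for 8 weeks". For both groups, "Use of additional lubricants is clarified and will be recorded".
- **Intervention (2.5.1).** "The therapy will occur thrice weekly for 8 weeks, each session lasting 30 min, culminating in 24 sessions". Some points lie around the eye: "Smaller needles (0.18 × 25 mm) are designated for EX-HN5, BL1, GB1, and BL2".
- **Ear seeds (2.5.1, text after Table 2).** "Post-acupuncture, auricular acupressure will be applied and maintained for 2 days", and "Auricular seeds will be replaced at the subsequent treatment session". Removing or covering them before an examination is not mentioned.
- **Masking (2.3).** "Outcome assessors and statisticians will remain blinded to group allocation". Section 2.6.2.11 adds that stored ocular surface images are read by two graders who know neither the arm nor the order of visits. Section 2.6.2.3 mentions masked assessors for corneal staining.
- **Timing (Table 1; 2.6.2).** Ocular surface tests are done at baseline, week 8 and week 12. Week 4 has questionnaires and the VAS only.

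**The concern.** The authors accept that a recent dose can distort a test, and they guard against it for drops. The same reasoning applies to a needling session around the eye, and the Discussion itself credits acupuncture with raising tear output. A participant who comes for treatment three times a week could be tested at week 8 straight after a session without breaking any stated rule, while a control participant could not be tested straight after a drop.

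The second strand is masking. Only the intervention arm wears ear seeds. An examiner facing the participant at the slit lamp can see them, and they identify the arm.

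At stake is the part of the evidence that masking can protect. Participants know their treatment, and OSDI, PSQI, SDS and SAS are all self-reported. The ocular measures are where a masked assessor adds something, and week 8 is the only on-treatment visit at which they are taken after baseline.

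**Working it through.** **1. What the pre-test rule does in each arm**

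| | Eye-drop arm | Acupuncture arm |
|---|---|---|
| Assigned treatment | Drops four times daily | Needling three times weekly, plus ear seeds |
| Does the 4-hour rule hold back assigned treatment? | Yes | No (it affects only any additional lubricant) |
| Stated interval from assigned treatment to test | 4 hours | None |

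The rule is symmetric in wording and asymmetric in effect.

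**2. Can a week-8 test follow a session on the same day?**
Table 1 marks intervention, ocular tests and VAS in the week-8 column, and section 2.7.2 has the VAS given after each session. That makes a shared visit plausible. It does not establish the order, and the VAS is also marked at baseline, so the column marks are not a same-day timetable. The text neither schedules a test after a session nor excludes it.

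**3. What an acute effect would do**
Let s be the mean acute shift in a tear measure shortly after a session, and p the share of intervention participants tested in that window. Controls have no counterpart, so

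observed difference = difference without the acute shift + p × s.

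If p = 0 nothing is added; if p = 1 the whole of s is added. The documents give neither p nor s, nor the sign of s for an acute effect, so no number can be put on this.

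**4. How often seeds are in place**
Inputs: 3 sessions a week for 8 weeks, and 2 days of wear per session (2.5.1).
- Plan's own figure: 3 × 8 = 24 sessions, which reproduces.
- Sessions at least 2 days apart: 3 × 2 = 6 days of 7, or 86%.
- Sessions on three consecutive days, seeds replaced each time (an assumption, as the spacing is not given): 1 + 1 + 2 = 4 days of 7, or 57%.
- Seeds left on until the next session replaces them: 7 of 7 days during the course.

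These figures describe wear. They equal the chance that seeds are present at the visit only if the visit falls at random within a treatment week. A visit just after a session raises that chance; a visit more than 2 days after session 24 lowers it.

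**5. Which outcomes are exposed**

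| Outcome at week 8 | Acute effect possible | Visible seeds can influence the reading |
|---|---|---|
| Fluorescein BUT, read live (2.6.2.1) | Yes | Yes |
| Corneal staining, scored at the slit lamp (2.6.2.3) | Not addressed in the text | Yes |
| Lid margin items (2.6.2.9), not listed among the analyzer measures | Not addressed in the text | Yes, if read live |
| TMH, by analyzer (2.6.2.7) | Yes | Little: instrument measure, masked image grading |
| Meiboscore, by analyzer with stored images (2.6.2.11) | Not addressed in the text | Little: masked image grading |
| OSDI (primary) | Not addressed in the text | Hardly: completed by an unblinded participant |

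Masked grading deals with the reader's expectation. It cannot undo a real short-lived change in TMH that is already in the image.

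**The case against.** The strongest reply is that this is a condensed article. The order of procedures within a visit, and how ears are concealed, would normally sit in the full protocol (version V3.0 is cited) or in the standard operating procedures mentioned in 2.7.1, neither of which is shown. That stands as a reason for moderate language. It does not dispose of the point: the article chose to state a pre-test rule with its reason, and that rule reaches one assigned treatment only. It also asserts assessor masking beside a seed-wear schedule that works against it.

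Several stronger readings are tempting and are not supported:

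- **That the rule applies to the eye-drop arm alone.** It is worded for all patients, and additional lubricants are not limited to one arm.
- **That bias and unmasking are established.** The text permits testing after a session but does not schedule it, and it gives no acute effect size. The Discussion's remark on tear output makes benefit to acupuncture the plausible direction for a tear measure; it does not prove it.
- **That all ocular outcomes lose their masking.** Stored images have masked graders with adjudication, and non-invasive break-up time is reported alongside the fluorescein reading.
- **That on-treatment visits in general are affected.** Only week 8 is. Week 4 has no ocular tests, and week 12 falls four weeks after treatment ends.
- **That 86% of assessments would reveal the arm.** That figure needs non-overlapping wear and randomly timed visits.
- **That the primary result is compromised by a seeing assessor.** OSDI is a questionnaire answered by participants whom the article already acknowledges as unblinded.

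**Conclusion.** The concern holds as a risk confined to the week-8 ocular secondary outcomes. As written, the plan guards against immediate effects of the assigned treatment in one arm only, and it leaves a live examiner likely to see which arm a participant is in. The acute-effect risk bears on BUT and TMH; the unmasking risk bears on fluorescein BUT, corneal staining and lid margin scoring.

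The size is unknown. The first risk equals p × s, with neither term in the documents. The second depends on how visits fall relative to sessions, with nominal wear between 57% and 86% of days under the 2-day rule, and more if seeds stay on until replaced. The conclusion assumes that no unshown procedure already fixes the session-to-test order or conceals the ears. It merits a change because the remedy is cheap and these are the outcomes for which masking is meant to count. It does not threaten the primary analysis.

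**What to change.** In section 2.6, next to the eye-drop rule:

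1. State that the week-8 ocular tests are done before any acupuncture session on the same day, and state a minimum interval since the last session.
2. Have someone other than the assessor cover both ears of every participant, in both arms, before the assessor enters. This is sturdier than relying on a 2-day gap: seeds are replaced at the next session, and removal once the 2 days are over is not stated, so a gap may not leave the ears bare. Covering also leaves the intervention itself unchanged.
3. Record time since last session and time since last drop in the CRF, so that adherence to the rule can be shown and a dependence on timing examined.

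If the full protocol or operating procedures already contain such steps, a sentence saying so is enough. No week-4 rule is needed, because no ocular tests are done then.

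The cost is a scheduling rule, ear covers and two CRF fields; some participants may need a test at a different time from a treatment visit. The article reports the trial as in its intervention phase, so the change can protect only week-8 visits still to come. For those already held, treatment logs and visit dates should at least show whether a session fell on the test day.
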